**A. Purpose of Protocol**

This study will test whether placebos without deception can result in clinical improvements in patients with allergic rhinitis.

The study aims to replicate previous findings and also examine possible mechanisms with respect to top-down and bottom-up mechanisms in open-label placebo experiments.

**B. Background for the Study**

Recent research has demonstrated that placebo treatment can have significant impacts for a wide variety of symptoms (Finiss et al., 2010). Unfortunately, in the traditional understanding response to placebos requires deception. This may cause problems with respect to patient-healthcare provider relationship and ethical difficulties. In contrast to this classic view recent research has demonstrated that placebos may work even without concealment. For example, Kaptchuk et al. (2010) conducted a randomized controlled trail including patients with irritable bowel syndrome. Half of the patiens received placebos without deception, the other half served as a control group. The authors found significantly higher mean global improvement scores, reduced symptom severity, and better quality of life scores for the open-placebo group. Similar results have been reported, for example, for patients with major depression (Kelley et al., 2012) and ADHD (Sandler et al., 2008).

Our previous study has demonstrated that open-label placebos also improve

symptoms in patients with allergic rhinitis (Schaefer et al., 2016). However, this pilot study was based on only few patients. Thus, we here want to replicate the results in a larger sample.

Furthermore, the mechanism of open-label placebo effects remains unclear. Are open-label placebo effects based on bottom-up mechanisms, such as classical conditioning? Or are they linked to raised expectancies about the positive effects of placebos in general, hence representing top-down effects? The latter may be related to the detailed information on the power of placebo effects. This information is included in nearly all open-label placebo studies. In order to disentangle top-down and bottom-up effects, we aim to manipulate this information: Half of the participants will be informed about the power of placebos, the other half not.

We expect to replicate the previous findings that open-label placebos improve allergic symptoms more than in a control group with comparable patient-healthcare provider relationships. Furthermore, we assume that the open-label placebo effect is independent of the information how powerful placebos are, thereby suggesting a bottom-up effect.

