**D. Hypothesis**

In allergic rhinitis patients, a two weeks course of open-label non-deceptive placebo treatment will be superior to no treatment plus usual care control. In addition, information on the positive effects of placebos will not interact with this open-label placebo effect.

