After signing the informed consent, patients will be informed about the power of placebos. They will be told that placebos are inactive substances and that they contain no medications. Although placebos contain no medication, placebo effects may still be powerful. The effect will be explained to them by pointing out that the body may automatically respond to taking placebo pills, like Pavlov’s dogs that salivated when they heard the bell. In addition, they will be told that a positive attitude may be helpful for the placebo effect, but is not necessary. Last, they will be instructed that those participants who will be in the placebo group need to take the placebos faithfully. These four statements are identical to the instruction used in previous studies on open-placebos. The further treatment is outlined above.

Description of the detailed information on placebo arms:

Same as before, but here the description of the power of placebos (as outlined above) will be omitted.

Randomization: Will be done by using sealed envelopes indicating the group assignment.

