**F. Data Analysis**

Outcome Measures: Two outcome measures will be used at baseline and endpoint of this study:

Allergic symptoms questionnaire:

Participants will be asked to assess their allergic symptoms by using a questionnaire describing different symptoms (itching, prickling, or burning feelings in the nose; constipated or running nose; impaired sense of smell or taste; sneezing fits; feeling like having a cold; itching or irritated skin; eczema on the skin; itching, burning or red eyes; billowed eyelids; itching, prickling or scratching feelings in the throat; sore throat; burning feeling or mucus in the mouth or throat; billowed mucosa; breathlessness; cough; headaches; feelings of exhaustion; lack of concentration; tiredness; disorders of the gastrointestinal tract). The patients will indicate their response on a seven-point scale ranging from ‘never’ (1) to ‘always’ (7). For further analysis we will calculate a composite score including all symptoms (see Schaefer et al., 2016). This is the primary outcome parameter.

Quality of Life (SF36): The SF-36 is a German version of the health survey developed by Ware and Sherbourne (1992) in order to examine subjective well-being and quality of life. This instrument assesses the quality of life with respect to the perception of the health both for patients and healthy people. It includes one multi-item scale that assesses different health concepts such as limitations in physical activities because of health problems, limitations in social activities because of physical or emotional problems, limitations in usual role activities because of physical health problems, bodily pain, general mental health (psychological distress and well-being), limitations in usual role activities because of emotional problems, vitality (energy and fatigue), and general health perceptions.

Planned Statistical Analyses

We will conduct analyses of variance (ANOVA) with three factors (time, placebos, information on the power of placebos) for allergic symptoms as well as for quality of life scores. In addition, we will test if baseline scores are different. All tests will be two-tailed with alpha set at .05.

Statistical Power

Based on effect sizes of our previous study (Schaefer et al., 2016), we will need 104 participants for an alpha set at .05. However, given that this is a pilot study and data collection is limited due to weather (pollen) conditions, we aim to include 60 patients in this study.

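### A null placebo-by-information interaction is read as suggesting a bottom-up mechanism, but expectancy, which defines the top-down route, is never measured

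*Protocol*

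**What the plan says.** Section B poses the mechanism question as a choice between conditioning (bottom-up) and expectancy: "Or are they linked to raised expectancies about the positive effects of placebos in general, hence representing top-down effects". It links expectancy to the talk only tentatively: "The latter may be related to the detailed information on the power of placebo effects". It then makes the talk the experimental lever: "In order to disentangle top-down and bottom-up effects, we aim to manipulate this information". The expected result and its interpretation are given in advance: "we assume that the open-label placebo effect is independent of the information how powerful placebos are, thereby suggesting a bottom-up effect".

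Section D turns the expected result into a hypothesis: "information on the positive effects of placebos will not interact with this open-label placebo effect". Section A names the examination of top-down and bottom-up mechanisms as part of the study's purpose. Section C is narrower and speaks only of the role of the information.

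On measurement, section F says: "Two outcome measures will be used at baseline and endpoint of this study". These are the symptom composite (primary) and the SF-36. Section E adds a daily diary of allergic complaints. No section contains an expectancy rating, a belief question or any other check that the talk did what it was meant to do.

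**The concern.** The inference from no interaction to bottom-up has a middle step: the talk must have produced a difference in expectancy between informed and uninformed patients. The protocol neither measures that step nor states it as an assumption, and its own wording treats the link from talk to expectancy as a possibility only.

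The talk is also not purely about expectancy. According to section E, patients are told that "the body may automatically respond to taking placebo pills", which is the conditioning account, and that a positive attitude helps but is not required.

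At stake is what the trial may conclude on a purpose named in section A. If the predicted null occurs, it could be reported as evidence against expectancy when expectancy had never been varied. Pre-treatment expectancy cannot be recovered afterwards, and no analysis plan can analyse data that were not collected.

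**Working it through.** **1. The inference, case by case.** Assume that the talk can alter the placebo effect only through expectancy. The expected placebo-by-information interaction is then:

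| | Placebo effect depends on expectancy (top-down) | Placebo effect does not depend on expectancy (bottom-up) |
|---|---|---|
| Talk changed expectancy | not zero | zero |
| Talk did not change expectancy | zero | zero |

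The two mechanisms differ only in the first row. In the second row a test at the two-sided 0.05 level (section F) is non-significant with probability 0.95 under either mechanism. To use a null as evidence for bottom-up, one must know that the trial is in the first row.

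**2. What the collected data can show.** The symptom composite, SF-36 and diary are all measures of response. None measures expectancy, so none identifies the row.

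**3. Precision of the interaction (a separate matter).** Inputs: 60 patients in four arms (section E); 15 per arm, which is an assumption because the allocation ratio is not stated; change from baseline with a common SD.

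- Standard error of the difference of differences: SD × √(4/15) = 0.516 SD.
- t quantile (0.975, 60 − 4 = 56 df): 2.003.
- Half-width of the 95% interval: 2.003 × 0.516 SD ≈ 1.03 SD.

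Even an estimate of exactly zero would rule out only interactions larger than about 1.03 SD. This figure reflects sample size. It does not measure the missing expectancy check.

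**4. The plan's own figure.** Section F gives 104 participants as the number needed. It cannot be reproduced, because neither the effect size nor the power is given. Solving backwards for a placebo main effect with an assumed power of 80% to 95% (1-df F test in the 2 × 2 design) gives a standardised effect of about 0.555 to 0.714. If that whole effect occurred in informed patients and none in uninformed patients, 60 patients would give power of about 0.18 to 0.27 for the interaction. A null would follow in about 73% to 82% of such trials. This is again a matter of precision.

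**5. What one expectancy item could detect.** Compare 30 informed with 30 uninformed patients (equal arms assumed), two-sided 0.05, 80% power. The normal approximation gives (1.960 + 0.842) × √(2/30) = 0.72 SD; the t-based calculation gives 0.74 SD. A strong effect of the talk on expectancy would probably show. A weaker one could be missed.

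**The case against.** The strongest reply is that the trial tests information, not expectancy. Sections C and D speak of information, it is a randomised factor, and it enters the three-factor ANOVA in section F. That test needs no expectancy measure. This stands in full. A reader might infer that the information comparison is invalid; the documents do not support that.

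Second, the wording is hedged. Section B assumes and suggests, and section F has no rule that turns a non-significant interaction into a verdict on mechanism. A reader might infer that the plan commits itself to concluding bottom-up whenever the talk makes no difference. It does not. The null at issue is also the interaction: a main effect of information without an interaction would still fit the prediction. The hedge softens the claim, but its direction is set in advance, and a failed manipulation gives that direction no support.

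Third, a reader might suppose that uninformed patients already hold high expectancy, because they volunteer and receive pills openly labelled as placebo. The documents give no figure for this, and the wording of the recruitment material and consent form is not shown. The point does not need it: it is enough that expectancy is unknown.

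Fourth, the script repeats the instruction of previous open-label placebo studies, and testing that customary information is a legitimate choice. That is so, but it supports a conclusion about the information and not about expectancy as such.

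Finally, a new item may do harm. Asking uninformed patients how much placebo pills will help puts to them an idea that the design withholds. It cannot be taken for granted that any priming would be equal across arms. This stands as a real cost.

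**Conclusion.** The concern holds for the mechanistic reading in section B and for nothing wider. As the trial is designed, a null placebo-by-information interaction cannot separate expectancy that does not matter from expectancy that was not changed. The randomised comparisons of placebo with no placebo, and of information given with information withheld, are unaffected.

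The conclusion rests on the protocol's own definition of top-down and on the absence of any expectancy measure among the data it lists. It does not depend on a numerical assumption. The half-width of about 1.03 SD (15 per arm assumed) is an added reason for caution. A reader might take it as the size of the missing check, but it would be the same if the talk were known to have worked. Equally, a larger sample would not repair the inference: a precise null with unchanged expectancy would still say nothing about mechanism.

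**What to change.** **Wording (needed, nearly free).** In section B, limit the conclusion from a null interaction to the effect of giving or withholding the information. State that the mechanism will be reported as unresolved unless two conditions are met: expectancy is shown to differ by information condition, and the confidence interval of the interaction excludes an effect that the sponsor has named beforehand as relevant. At 60 patients the second condition can hardly be met for a margin below about 1 SD, so the sponsor should expect an unresolved mechanism even if the talk worked.

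**Measurement (if the mechanism question is to be answerable).** Add one self-rated expectancy item for all patients, after the talk or its omission and before the first pill. Report the difference between information conditions with its confidence interval. A non-significant difference should not be read as proof that the talk failed, since only differences of about 0.74 SD or more are detectable with 80% power.

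**Cost.** One questionnaire item at an existing visit and a short paragraph of text; no extra visits or patients. The drawback is priming, possibly stronger in the uninformed arms, which could shrink the contrast under test. If the sponsor judges that risk too high, the wording change alone is enough to make the conclusion sound.

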**C. Aim**

Replication of earlier results if placebos without deception reduce symptoms in patients with allergic rhinitis (Schaefer et al., 2016) and proof of the role of detailed information on how powerful placebos are for this effect.

**D. Hypothesis**

In allergic rhinitis patients, a two weeks course of open-label non-deceptive placebo treatment will be superior to no treatment plus usual care control. In addition, information on the positive effects of placebos will not interact with this open-label placebo effect.

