**E. Description of Research Protocol**

Overview: This study aims to test whether non-deceptive administration of placebo in patients with allergic rhinitis will be superior to a control group, and if this effect is independent of detailed information on positive effects of placebos.

Design: 60 patients with allergic rhinitis will be randomized to a two-week course of either non-deceptive placebo pill with detailed information on positive effects of placebos, of non-deceptive placebo pill without detailed information on positive effects of placebos, of no treatment plus usual care with detailed information on positive effects of placebos, and of no treatment plus usual care without detailed information on positive effects of placebos. All groups will receive the same amount of time with the practioner. Participants will be assessed at baseline and at the end of the two weeks.

Design and intervention:

Description of the open-label placebo treatment arms:

After signing the informed consent the patients will be assessed with respect to their allergic symptoms and quality of life. They will be told to note their allergic complaints at the end of each day in an allergic diary. Then they will receive 28 placebos in a white box, labeled with the logo of the university and the following information “Placebo pills (28), take one in the morning and one before night, for 14 days”

Description of the no treatment usual care control arms:

This control group will be treated as the open-placebo group, but do not receive any placebos. The purpose of this control group is to match for time with practioner and to assess general improvements of allergic symptoms due to changes in weather (pollen) conditions.

Description of the detailed information on placebo arms:

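### The second hypothesis predicts no interaction, but the only test bearing on it is a two-tailed difference test at .05, and a non-significant result with 60 patients does not support that prediction

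*Protocol*

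**What the plan says.** Section D (Hypothesis) states two predictions. The first is that open-label placebo is superior to control. The second is a prediction of no effect: "In addition, information on the positive effects of placebos will not interact with this open-label placebo effect". Section E (Overview) repeats it as a study question: "if this effect is independent of detailed information on positive effects of placebos". Section B (Background) says what would be concluded: "we assume that the open-label placebo effect is independent of the information how powerful placebos are, thereby suggesting a bottom-up effect".

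Section F (Planned Statistical Analyses) gives the analysis: "We will conduct analyses of variance (ANOVA) with three factors (time, placebos, information on the power of placebos", applied to allergic symptoms and to quality of life, with a comparison of baseline scores. It adds: "All tests will be two-tailed with alpha set at .05". Under Statistical Power, "we will need 104 participants for an alpha set at .05", but the trial aims for 60. The stated reasons are that it is a pilot and that the pollen season limits data collection. Section F gives neither the effect size nor the power behind the 104, and does not say which contrast it was calculated for.

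**The concern.** In this ANOVA the second hypothesis corresponds to the time by placebo by information term. The null hypothesis of that term is that information does not modify the placebo effect, which is exactly what Section D predicts. The test can count against the prediction but cannot count for it: a large p-value arises equally from a true absence of interaction and from too little data. The less precise the trial, the more easily the hypothesis appears to be borne out.

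At stake are one of the two stated hypotheses and the mechanistic reading in Section B. That reading has a further weakness. The information script in Section E itself explains conditioning and tells patients that a positive attitude is not required. An absent interaction could therefore also mean that the script did little to change expectations.

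**Working it through.** **Inputs.** From the protocol: planned N = 60, four groups, half of the patients informed, two-sided alpha .05, and a stated requirement of 104. Assumed: an equal split, 15 per cell; effects in units of the SD of the change score; 80% power behind the 104.

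**The plan's own figure.** The 104 cannot be reproduced, because neither effect size nor power is given. It can only be solved backwards at the assumed 80% power:

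- 52 against 52: d ≈ √(2/52) × (1.960 + 0.842) = 0.549; with the t distribution, 0.555.
- 26 against 26 (two cells of four): d ≈ √(2/26) × 2.802 = 0.777; with the t distribution, 0.792.

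These are assumptions and not figures from the document. At 90% or 95% power, the 52-against-52 layout would imply 0.64 or 0.71, inside the same range.

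**Precision of the interaction.** With two time points, the three-way term equals the two-way interaction on change scores: (placebo − control, informed) − (placebo − control, uninformed).

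- SE = SD × √(4/15) = 0.516 SD, with 60 − 4 = 56 df.
- 95% CI half-width = 2.003 × 0.516 = 1.03 SD.
- 90% CI half-width = 1.673 × 0.516 = 0.86 SD.

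**Scenario: information is essential.** The placebo effect is d with information and 0 without, so the interaction equals d. Treating the earlier effect as an informed effect is reasonable, because Section E says the script matches the one used in earlier open-placebo studies.

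| | d = 0.555 | d = 0.792 |
|---|---|---|
| Noncentrality, d/0.516 | 1.07 | 1.53 |
| Power of the interaction test (noncentral t, 56 df) | 18% | 33% |
| Interaction non-significant | 82% | 67% |

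**How often this would look like a placebo effect independent of information.** Calling an effect independent presupposes that an effect was found. In this scenario the averaged placebo effect is d/2, with SE = 2/√60 = 0.258 SD. Its ratio to its SE is therefore the same as for the interaction, and so is its power: 18% and 33%. The two estimates are independent apart from the shared residual variance, so the joint probability is close to the product:

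- d = 0.555: 0.183 × 0.816 = 0.149; allowing for the shared variance, 14.7%.
- d = 0.792: 0.325 × 0.674 = 0.219; allowing for the shared variance, 21.5%.

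As a share of the trials with a significant effect in favour of placebo: 14.7/18.3 = 80% and 21.5/32.5 = 66%.

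**Could 60 patients support independence at all?** If the estimated difference were exactly 0, the 90% CI would still reach ±0.86 SD. That is larger than the whole placebo effect implied by the 104 under either layout.

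**The case against.** - **The protocol calls itself a pilot and admits 60 against 104.** This explains the imprecision and is openly stated. It does not turn imprecision into evidence of no interaction. A larger sample alone would not cure the mismatch either: at 104 patients the SE is √(4/26) = 0.392 SD, power for a 0.55 SD interaction is about 29%, and a difference test still cannot affirm its null.
- **The wording is cautious.** This stands. Section B speaks of an assumption and of a suggestion. A reader might infer that the sponsor would present a non-significant term as proof of independence, and might cite Section C, which announces "proof of the role of detailed information on how powerful placebos are for this effect". That phrase leaves open whether information has a role, and Section F contains no rule that p > .05 establishes independence. Even so, an interval of about ±1 SD does not support a suggestion.
- **An equivalence margin or interval criterion may be in the SAP.** This also stands, so their absence is not the point here. The mismatch lies in what the protocol itself fixes: a no-effect hypothesis, a difference test and the conclusion to follow.
- **The effect sizes are back-calculated.** Correct. The logical point does not depend on them, and the interval widths depend only on 15 per cell. The error rates do depend on them and are therefore shown as a range.

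**Conclusion.** The point holds: as written, the analysis cannot support the second hypothesis, and following it would let imprecision pass as support. The interval for the difference in placebo effects would be about ±1.03 SD. If information were essential, the interaction would be missed in 67% to 82% of trials.

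A reader might infer from the last figure that the trial would report independence in most cases where the effect depends wholly on information. The documents do not support that. The hypothesis concerns an existing placebo effect, and in this scenario the placebo effect is itself usually missed. The misleading pair of results occurs in about 15% to 21.5% of all trials. The 66% to 80% applies only to trials that find a placebo effect.

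The logical point is firm. The percentages rest on 15 per cell, 80% power behind the 104, and an earlier effect obtained with information given. The comparison of placebo with control under the first hypothesis is not affected.

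**What to change.** 1. In Sections D and F, state that a non-significant interaction will not be taken as independence.
2. In Section F, make the reported result for this aim the difference between the informed and uninformed placebo effects on change in the symptom score, with its 95% CI. Report the placebo effect in each information group alongside it, whatever the interaction p-value.
3. Call this aim exploratory estimation, and note that 60 patients cannot exclude differences below about 0.86 SD (90% CI, estimate at zero). A formal equivalence margin at, say, half the implied placebo effect (about 0.28 to 0.40 SD) could not be met at this size, so adding one would not help.
4. In Section B, replace the closing inference to a bottom-up mechanism with a statement limited to the differences that the confidence interval excludes.

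The cost is a few sentences of protocol text and a few lines of analysis, with no extra patients. The sponsor gives up a mechanistic claim that the design cannot support. The change should be made before the data are analysed, because the same restriction adopted afterwards would carry less weight.
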